## Description of Statistical Methods

The risk of clinically significant upper-gastro-intestinal bleeding and image-proven cerebral bleeding by 60 days will be summarized as x/n (%) in each group together with two-sided 95% Wilson confidence intervals and corresponding confidence intervals for risk differences between groups.

The risk of the primary efficacy endpoint of new MRI-proven brain infarction or death by 60 days will be summarized in the same way. In addition, we will perform a linear trend test for group differences based on logistic regression with adjustment for gender, MRC grade, and age.

The risk of disability or death will be summarized as for the primary efficacy endpoint and the analysis of overall survival during 240 days will be based on Kaplan-Meier graphs and Cox regression. The frequency of adverse events in each study arm and resolution of CSF inflammation will be analysed descriptively.

Analyses to explore the effect of LTA4H genotype will include this information as an additional covariate in the regression models.

As this is a pilot study of relatively small size and limited power, p-values will be interpreted with caution and a one-sided p-value <0.1 will be regarded as mild evidence for an effect. Corresponding two-sided 95% confidence intervals will be provided for all tests to assess the range of plausible magnitudes of effects given the data.

No imputation of missing data will be performed. For the analysis of GI/cerebral bleeding by day 60, patients lost to follow-up before day 60 (without prior GI bleeding) will be excluded from the analysis to get a conservative estimate of the true proportion of bleeding in the aspirin groups. The analysis of the primary efficacy endpoint will exclude patients with missing baseline or follow-up MRI scans (except for prior death).

All analyses will analyze patients according to their randomized treatment group.

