### Randomisation and Dosing

Randomisation will be 1:1:1 to 81mg aspirin, 1000mg aspirin and placebo, with stratification by MRC disease severity grade. Subject numbers will be stratified and assigned sequentially as each subject is randomised. Each patient will receive the next sequential package of blinded study drugs which will be prepared in advance and available on the ward. Each treatment pack will contain two bottles of study treatment. One bottle will contain 81mg tablets of aspirin or placebo, the second bottle will contain 500mg tablets of aspirin or placebo. For 60 days, patients will take one 81mg tablet and two 500mg tablets. Administration of the two daily 500mg tablets will be separated by approximately 12 hours.

The first dose of one 81mg tablet and one 500mg tablet will be given as soon as possible after randomisation. One 500mg tablet will be taken approximately 12 hours later. In the case of the first dose being taken late in the day on study day one, the second dose may be given over a shorter time period to ensure the full dose is administered on the first day.

Patients will take medication orally with water if required. Patients unable to swallow will be given crushed tablets via a naso-gastric tube at the same doses.

Patients who vomit within 30 minutes of dosing will be given a replacement dose.

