# STUDY TREATMENT

## Description of Study Treatment

An independent trial pharmacist will generate a randomization list stratified by site and MRC grade, with treatment assignments in blocks of varying size. Based on this list, identical treatment packs will be created and distributed to the wards. Each treatment pack will contain two bottles. The first bottle will contain 60 tablets of either 81mg aspirin or matched placebo. The second bottle will contain 120 tablets of either 500mg aspirin or matched placebo. Additional pills will be added to bottles to allow for accidental discards, replacement of vomited doses and to limit manipulation of compliance pill counts. All patients will take one 81mg tablet and two 500mg tablets per day. Administration of the two daily 500mg tablets will be separated by approximately 12 hours. Treatment allocation will be as follows:

Arm A: 81mg aspirin – one tablet 81mg aspirin, two tablets 500mg-matched placebo (bottle #1 is aspirin, bottle #2 is placebo)

Arm B: 1000mg aspirin – one tablet 81mg-matched placebo, two tablets 500mg aspirin (bottle #1 is placebo, bottle #2 is aspirin)

Arm C: placebo – one tablet 81mg-matched placebo, two tablets 500mg-matched placebo (bottle #1 and #2 are placebo)

Daily treatment of one 81mg size tablet and two 500mg size tablets (1000mg in two divided doses) will be taken for 60 days.

The 81mg tablets and 500mg tablets will not be visually matched, hence the need for patients to take both tablets for each dose. All tablets will be coated to prevent taste differentiation between active drug and placebo.

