# STATISTICS

## Sample size justification

Sample size was chosen based on clinical and feasibility considerations. The calculations below provide evidence of what can be achieved with a sample size of 40 patients per group for the primary safety and efficacy endpoints, respectively.

The proportion of HIV uninfected patients with clinically significant gastro-intestinal bleeding from our on-going 05TB trial of hyper-intensive anti-tuberculosis chemotherapy in Vietnam is about 1% (3/278). Cerebral bleeding associated with TBM is extremely rare (estimated at <0.01% of all patients), but it is possible it may be more common in those treated with aspirin. We have, therefore, included in the primary assessment of safety.

Assuming no effect of aspirin on gastrointestinal bleeding, i.e. a true gastrointestinal bleeding risk of 1% for aspirin, the probability will be 67% to observe 0/40 patients and 27% to observe 1/40 patient experiencing gastrointestinal bleeding in each aspirin arm. The corresponding upper limits of the 95% confidence intervals for the risk of a gastrointestinal bleed would allow “proving” that the true gastrointestinal bleeding risk for aspirin is (at worst) ≤8.8% (in case of 0/40 observed gastrointestinal bleeding) or ≤12.9% (in case of 1/40 observed gastrointestinal bleeding).

Assuming further equal gastrointestinal bleeding risks of 1% in the combined aspirin groups, the probability will be 80% that we observe zero or one bleeding event amongst the 80 patients receiving aspirin and the corresponding upper limit of the 95% confidence interval for the risk of a bleed would allow “proving” that the true overall bleeding risk for aspirin is (at worst) ≤6.8%.

If in contrast, the risk of bleeding was increased to 10% in one of the aspirin arms, the probability would be 78% that we observe 3/40 patients with gastrointestinal bleeding or more with a corresponding 95% confidence interval that would “prove” that the true bleeding risk for that aspirin arm were (at best) ≥2.5%.

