We expect a risk of new MRI-proven brain infarction or death within 60 days of approximately 40% in the control arm. Based on the results of the trial performed by Misra et al ^16^, we assume that 81 mg aspirin daily may halve this risk to 20% and the risk in the 1000 mg aspirin daily arm is between 20-40%, then a linear trend test across the 3 groups will have approximately 75% power to detect such an effect at the one-sided 10% significance level (i.e. to generate “mild evidence”) and approximately 50% power to detect it at the conventional one-sided 2.5% significance level.

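### Risk-difference intervals for efficacy and for disability or death ignore MRC grade, the randomisation stratum: valid, but wider than needed if grade is prognostic, and almost free to improve

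*Protocol*

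**What the plan says.** MRC grade is built into the allocation. Section 6.4.5 states: "Randomisation will be 1:1:1 to 81mg aspirin, 1000mg aspirin and placebo, with stratification by MRC disease severity grade". Section 7.1 adds: "An independent trial pharmacist will generate a randomization list stratified by site and MRC grade". The design summary (section 5.1) also names site and grade, but only one recruiting hospital is identified, so grade is the stratum that matters.

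Section 9.2 uses grade in one analysis, the logistic trend test for the primary efficacy endpoint, alongside gender and age. Bleeding risk is summarised by arm as counts and percentages with Wilson intervals and "corresponding confidence intervals for risk differences between groups". The primary efficacy endpoint is to be summarised likewise, and disability or death follows the efficacy endpoint. No stratification is attached to any of these intervals.

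For survival, a secondary endpoint, the text is only that "the analysis of overall survival during 240 days will be based on Kaplan-Meier graphs and Cox regression". No covariates are listed and none are ruled out. Section 9.2 then says that LTA4H genotype will be added as a further covariate to the regression models, in the plural.

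**The concern.** If the stratification factor predicts outcome, balancing on it removes part of the chance variation between arms. An interval computed as if allocation had been unstratified does not take credit for that, so it covers more than its nominal 95% and is wider than the data justify.

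This matters more than usual here because section 9.2 plays down p-values and relies on 95% intervals to show which effect sizes remain plausible. Those intervals are what a definitive trial would be planned from. For disability or death, the crude summary is the only analysis named, although preventing neurological sequelae is the stated motive for the trial (section 3).

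**Working it through.** **The plan's own figure.** Section 9.1 describes "what can be achieved with a sample size of 40 patients per group" and gives about 75% power at one-sided 10% and 50% at one-sided 2.5% for the trend test. With risks of 40%, 30% and 20% in groups of 40, and scores ordered by assumed risk, a simulated Cochran-Armitage test gives 74.7% and 50.1%. The figure reproduces. That test is already adjusted for grade, so nothing below changes it.

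**Inputs.** From the protocol: 40 per arm, 1:1:1, stratified by grade. Assumed, because the protocol does not give them: grade mix 35/40/25%; control risk by grade (I/II/III) as in the table; within-grade hazard ratio 0.5, so that active risk = 1 - (1 - control risk)^0.5.

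**Risk difference, formulas.** With overall risks p1 and p0, grade shares w and grade-specific risks p1g and p0g:

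- crude variance = [p1(1-p1) + p0(1-p0)]/40
- stratified variance = Σ w[p1g(1-p1g) + p0g(1-p0g)]/40
- excess width = √(crude/stratified) - 1

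**Worked case, control risks 10/25/55%.** Active risks are 5.1/13.4/32.9%; overall risks are 27.25% and 15.38%.

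- Crude sum: 0.2725×0.7275 + 0.1538×0.8462 = 0.1982 + 0.1302 = 0.3284; SE = √(0.3284/40) = 0.0906.
- Within-grade sum: 0.1684 + 0.1187 = 0.2870; SE = √(0.2870/40) = 0.0847.
- Excess: 0.0906/0.0847 - 1 = 7.0%.

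| Control risk by grade | Crude SE | Stratified SE | Crude too wide, HR 0.5 | Crude too wide, no effect |
|---|---|---|---|---|
| 30/30/30% (flat) | 0.0931 | 0.0931 | 0% | 0% |
| 15/25/45% (moderate) | 0.0893 | 0.0867 | 3.0% | 3.6% |
| 10/25/55% (strong) | 0.0906 | 0.0847 | 7.0% | 8.5% |
| 15/40/75% (very strong) | 0.1029 | 0.0929 | 10.8% | 13.1% |

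This closed form is slightly generous. The usual crude SE divides by n rather than n-1, which makes it smaller by a factor √(39/40) = 0.987, while small strata need the n-1 divisor. Simulation with stratified blocks then gives stratified intervals narrower by about 1-2% (moderate), 5-7% (strong) and 8-11% (very strong). In the strong case at HR 0.5, the mean crude SE was 0.0895 and the stratified SE 0.0851, against an actual standard deviation of 0.0856. A separate check at 40% versus 20%, the protocol's efficacy assumption, found crude SEs too large by about 0%, 6% and 15% for weak, strong and very strong gradients.

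**Bias and coverage.** The estimate does not move: the mean risk difference was -0.120 by both methods (strong) and -0.154 by both (very strong). The unstratified Newcombe interval covered 96.1-97.6% when grade was prognostic and 95.0-95.2% when it was not.

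**Safety endpoint.** At the protocol's 1% bleeding risk, 40×0.01 = 0.4 events are expected per arm. There is nothing useful to stratify.

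**Cox model.** 81 mg versus placebo, 6,000 simulated trials per scenario, censored at day 240, true within-grade HR 0.5; without and then with grade as strata:

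| Gradient | Median HR | Power, one-sided 10% | Power, one-sided 2.5% | Mean SE of log HR |
|---|---|---|---|---|
| Moderate | 0.505 → 0.494 | 51.4 → 52.6% | 22.6 → 24.6% | 0.548 → 0.550 |
| Strong | 0.519 → 0.494 | 50.6 → 54.0% | 21.1 → 25.4% | 0.531 → 0.533 |
| Very strong | 0.541 → 0.500 | 60.6 → 66.8% | 29.2 → 38.4% | 0.417 → 0.422 |

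The HR moves by 0.011, 0.025 and 0.041. The SE does not fall. With a flat gradient nothing changes.

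**The case against.** The strongest reply is that no analysis here is invalid. The crude intervals err on the cautious side, accompany descriptive summaries, and belong to a pilot that admits limited power. That stands, and it is why this is an improvement rather than an error.

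Four stronger readings are tempting, and the protocol does not support them.

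- *A reader might infer that the Cox model is planned without grade.* The text is silent. The plan to add genotype to regression models in the plural fits models that already have covariates, and the covariate list of a secondary model is normal SAP content.
- *A reader might infer that the crude risk differences understate the effect.* They do not. The risk difference is collapsible, so under randomisation the crude estimate is unbiased for the overall difference. Only the hazard ratio shifts, because the marginal and within-grade hazard ratios are different quantities.
- *A reader might infer that adjusting would narrow the hazard-ratio interval.* The unadjusted SE is conservative (0.417 against an actual 0.383 in the very strong case), but stratifying leaves it essentially unchanged. The gain comes from the estimate moving away from 1.
- *A reader might infer that the trial's stated power is eroded.* The only power figure belongs to the trend test, which is already adjusted for grade.

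**Conclusion.** The point holds in a limited form. As written, the risk-difference intervals for the primary efficacy endpoint and for disability or death do not use the randomisation stratum. They are unbiased and valid, and wider than necessary by roughly 0-2% for a weak to moderate gradient (about 3% by the closed form before the small-sample correction), 5-7% for a strong one and 8-15% for a very strong one. If grade does not predict outcome, the excess is zero.

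For the secondary survival model, this is a request to state what the protocol leaves open. Including grade would reduce attenuation of the hazard ratio by about 0.01-0.04 and add about 1-6 points of power at one-sided 10% (2-9 at one-sided 2.5%).

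All these sizes rest on an assumed grade mix and assumed risks by grade. The direction does not, provided grade is prognostic. Minor severity; a free improvement.

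**What to change.** For the primary efficacy endpoint and for disability or death, add risk differences stratified by MRC grade (for example Mantel-Haenszel-weighted) with stratified confidence intervals. Keep crude counts and percentages with Wilson intervals for display. Leave the bleeding endpoint crude.

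State that the 240-day Cox model includes MRC grade, as strata or covariate, together with age and gender, to match the logistic model.

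The cost is a few lines of analysis text and a little extra programming. Grade must be known at randomisation, so no new data are needed. The drawback is small strata: with a 25% share, the smallest grade would have 120×0.25/3 = 10 patients per arm, so the interval method should tolerate sparse cells.

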**Figure 1. LTA4H genotype modulates susceptibility to mycobacterial infection**

*
[figure not shown]
*

Zebra fish at both poles of the inflammatory response (minor and major allele homozygotes) were unable to control mycobacterial replication within granulomas, whereas those fish with an intermediate inflammatory response (the heterozygotes) controlled the infection. The phenotype of the homozygous fish could be changed to that of the heterozygotes through the respective addition of pro-inflammatory leukotriene B4 (LTB4) or TNF-α to LTA4H low fish, or by inhibition of TNF-α in the LTA4H high fish by either aspirin or dexamethasone [^19^](#_ENREF_19). Furthermore, in Vietnamese adults recruited to the earlier dexamethasone trial, only major allele homozygous adults with the hyper-inflammatory phenotype benefited from dexamethasone (**Figure 2**). Indeed, dexamethasone treatment of those with a hypo-inflammatory phenotype appeared to be detrimental.

**Figure 2. LTA4H genotype influences survival from TBM in all patients (A), pre-treatment CSF leucocyte counts (B), and survival in those who did not (C) and did (D) receive adjunctive dexamethasone.**

[figure not shown]

These findings need replication in a different population, and such studies are currently underway at OUCRU, but they provide an elegant potential explanation for the previous failure to find the mechanism by which corticosteroids improve survival from TBM in Vietnamese adults. They also have important implications for the current pilot study and we will investigate the influence of LTA4H genotype on aspirin’s effect on CSF inflammation and clinical outcome.

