**Why do we need this pilot study?**

There are several outstanding questions that need to be addressed by a pilot study before embarking on a large, definitive, randomised controlled trial of adjunctive aspirin for TBM. These are:

1. What is the safety and tolerability of 81mg and 1000mg dose aspirin when added to dexamethasone for the first 60 days of treatment of TBM?
2. Does aspirin at these doses reduce MRI-proven infarction and neurological sequelae or death?
3. Does 81 mg aspirin daily have the same anti-inflammatory effect as 1000 mg aspirin daily (assessed by measurement of CSF prostaglandins) and which dose is likely to be most effective?
4. How does host genotype (in particular, LTA4H genotype) influence the anti-inflammatory, anti-thrombotic, and clinical effects of aspirin?

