## Summary of Trial Design

The study is a parallel group, double blind, randomised, placebo controlled trial of 60 days of placebo vs. 81mg daily dose vs. 1000mg daily dose aspirin for the treatment of HIV-uninfected adults with tuberculous meningitis (see trial schema in appendix A). Patients will be recruited at the Hospital for Tropical Diseases (HTD), Ho Chi Minh City, Vietnam and should not have had more than 2 days of anti-tuberculosis chemotherapy or have received aspirin or any other NSAID within 2 weeks of randomisation. They should be able to have an MRI of their brain within 5 days of randomization.

Once enrolled, patients will be followed for 60 days and followed up at 8months for final outcome. They will all receive standard anti-tuberculosis chemotherapy and adjunctive dexamethasone (for 6-8 weeks), according to respective National Tuberculosis Programme guidelines (see attached guidelines for Viet Nam with this protocol). Participants will be stratified by site and MRC disease severity grade, and randomised on entry to one of three arms (1:1:1 ratio): aspirin 81mg, aspirin 1000mg or placebo daily for 60 days. Patients will be in-patients for at least the first 14 days of study treatment enabling real-time active surveillance of any adverse events after which they will be discharged according to clinical care. Study drug and standard treatment may be continued while patients are followed as out-patients.

Lumbar puncture will be performed before the start of treatment and then repeated in all patients on day 30 and 60 as per normal clinical care. Blood draws for pharmacokinetic assessment will be done 5 times between days 1 and 14. Assessment of peripheral blood monocyte/macrophage antimicrobial activity will be made at baseline and on day 240.

Clinical assessments will be performed at enrolment and weekly between day 7 and discharge. Brain magnetic resonance imaging (MRI) will be performed at baseline, day 60 and 240. A final clinical assessment of neurological disability will be made at 240 days.

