## Primary and Secondary Endpoints/Outcome Measures

The primary safety endpoint will be the occurrence of clinically significant upper-gastro-intestinal bleeding and any cerebral bleeding confirmed by brain imaging by 60 days from randomisation.

Clinically significant upper gastro-intestinal bleeding will be defined as any one of the following:

1. Vomiting fresh or changed blood of any volume
2. Melena
3. Unexplained drop in haemoglobin concentration of >2g/L
4. Greater than 5mls of fresh or changed blood aspirated from nasogastric tube

The primary efficacy endpoint will be any new MRI-proven brain infarction or death by 60 days. To assess this endpoint MRI will need to be taken at baseline and at 60 days from randomisation. The scans will be read by an independent neuroradiologist blind to the treatment allocation.

The secondary endpoints will be:

- Number of grade 3&4 and serious adverse events by day 60 from randomisation
- Time to death during 240 days from randomisation
- Duration of hospital stay
- Neurological disability (as assessed by the modified Rankin score and Glasgow outcome score) by days 60 and 240.
- Resolution of CSF inflammation by day 30 through measurement of CSF leucocytes, protein, glucose, cytokines (TNF-α, IL-1β, IL-8, IL-10, IFNγ) and eicosanoids (15-epi-Lipoxin, Lipoxin A4, LTB4, PGE2, TBXB2, PGD2).
- Antimicrobial activity of peripheral blood monocyte/macrophages on day 240 compared to baseline.
- The proportion of patients with MRI-proven infarction by day 240
- Concentration-time profile of salicylic acid including exposure, peak levels, half-life, elimination clearance and volume distribution

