### Screening and Eligibility Assessment

Potential participants will be screened by the attending physicians. Screening will include the CSF analysis results of the standard diagnostic lumbar puncture and GeneXpert MTB/RIF test when available. Any residual volume of CSF remaining from this lumbar puncture will be stored for the purposes of this study. The results of an HIV test (performed routinely on all patients admitted to the ward) will also be available at screening. Results of any tests performed for clinical care during this illness episode may be used for the purposes of screening. Residual volumes of samples drawn for clinical care during this illness episode may be tested or stored for analysis detailed in this protocol. Results of tests on cerebrospinal fluid obtained within 7 days of randomization and results on blood obtained within 2 days of randomization may be applied to meet inclusion/exclusion criteria.

A screening log will be kept on the ward, with a record of all patients screened and how they met/did not meet the study entry and exclusion criteria. Patients who do not meet the study criteria will be informed as such and treated as per best available clinical care.

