### Subsequent Assessments

The outline of study assessments is provided in appendix B.

Follow-up clinical assessments should be made weekly until discharge from hospital. The assessments will include careful neurological examination and proactive surveillance for symptoms and signs of aspirin toxicity/adverse reactions (e.g. gastritis, tinnitus, gastrointestinal bleeding, renal impairment). All adverse events will be documented, followed and assessed for the likelihood of being related to aspirin.

A full blood count, and measurement of plasma urea, creatinine, electrolytes and stool microscopy for red blood cells will be taken on each clinical assessment day, day 30 and day 60 (5mls EDTA blood; 5mls clotted blood). Patients will have 20mls of heparinised blood taken at day 240 for assessment of the antimicrobial activity of peripheral blood monocytes/macrophages. Whole blood (2ml) will be obtained at 5 time points during the first 14 days of study treatment and analysed to assess the pharmacokinetic characteristics of aspirin.  Time points will be randomly assigned to a range of periods after drug dosing. A concentration-time profile of salicylic acid including exposure, peak levels, half-life, elimination clearance and volume distribution will be analysed.

Patients will have lumbar punctures on days 30 and 60, as per normal clinical care of patients with TBM in the hospital. 10mls of CSF should be taken when possible (as per normal care) and standard biochemical and microbiological tests performed (including mycobacterial smear and culture and GeneXpert MTB/RIF on all specimens collected during the study period). The CSF supernatant should be stored immediately at -80^0^C for later analysis of cytokine and eicosanoid concentrations.

A full clinical examination, brain MRI and neurological disability assessment by the Glasgow coma score and the Modified Rankin score will performed on days 60 and 240.

Window periods for all study procedures will be: +/- 2 days for any procedure scheduled for day 7, 14, 21, 28; +/- 5 days for any procedure scheduled on day 30 – 60; and +/- 14 days for any procedure scheduled for day 240. Screening, enrolment and day 1 schedule windows are as detailed in the appropriate sections of this document.

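### Section 9.2 plans no between-dose estimate and no regression model for CSF inflammation, although section 3 asks a dose question and a genotype question that need them

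*Protocol*

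**What the plan says.** Protocol section 3, under the heading on why the pilot is needed, lists the questions to settle before a definitive trial. The third is: "Does 81 mg aspirin daily have the same anti-inflammatory effect as 1000 mg aspirin daily (assessed by measurement of CSF prostaglandins"; it goes on to ask which dose looks the more effective. Earlier in section 3, the part on LTA4H states that "we will investigate the influence of LTA4H genotype on aspirin’s effect on CSF inflammation and clinical outcome".

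Section 5.2 makes this a secondary endpoint: "Resolution of CSF inflammation by day 30 through measurement of CSF leucocytes, protein, glucose, cytokines" and eicosanoids, among them PGE2 and PGD2.

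On sampling, section 5.1 says "Lumbar puncture will be performed before the start of treatment and then repeated in all patients on day 30 and 60". For the diagnostic puncture, section 6.4.3 says "Any residual volume of CSF remaining from this lumbar puncture will be stored for the purposes of this study". At follow-up, section 6.4.6 says "10mls of CSF should be taken when possible".

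The analysis in section 9.2 is one sentence: "The frequency of adverse events in each study arm and resolution of CSF inflammation will be analysed descriptively". On genotype, the same section says: "Analyses to explore the effect of LTA4H genotype will include this information as an additional covariate in the regression models".

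**The concern.** The third rationale question is a contrast between two randomised arms, and it is meant to inform the choice of dose for a larger trial. Arm-by-arm summaries show each arm's level. They do not by themselves say how far apart the doses are, or how uncertain that distance is.

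The genotype aim has a similar problem. Genotype is to enter the regression models as a covariate, but section 9.2 names no regression model for CSF, so as written there is nothing for it to enter.

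This is more than detail left to a SAP, because the protocol has chosen a method. In the same section the bleeding, primary efficacy and disability endpoints get intervals for risk differences, and survival gets Cox regression. Section 9.2 also promises intervals to accompany tests, but CSF has no test.

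At stake is whether the pilot reports a usable dose comparison on samples it is already collecting. A further risk is that the markers to emphasise are picked after the data are seen.

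**Working it through.** The protocol gives no power or precision figure for CSF, so there is none to reproduce. The check asks whether an estimate is feasible at the planned size and what the baseline value would add.

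**Inputs**
- n = 40 per arm (section 9.1; 120 patients, 1:1:1).
- ρ, the correlation between baseline and day-30 log marker: not in the protocol, assumed 0.3, 0.5 and 0.7.
- Results are in units of the marker's SD on the log scale, because the protocol gives no SD.
- Complete sampling at first, then 28 per arm as an assumed shortfall.

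**1. Precision of 1000 mg v 81 mg**

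Half-width of the 95% interval = 1.96 × √(1 − ρ²) × √(2/n). With n = 40 and no adjustment this is 1.96 × √(2/40) = 0.44 SD.

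| n per arm | unadjusted | ρ = 0.3 | ρ = 0.5 | ρ = 0.7 |
|---|---|---|---|---|
| 40 | 0.44 | 0.42 | 0.38 | 0.31 |
| 28 | 0.52 | 0.50 | 0.45 | 0.37 |

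For an assumed true difference of 0.5 SD with 40 per arm, power at the protocol's own one-sided 10% level is 83% unadjusted and 90% at ρ = 0.5. At two-sided 5% it is 61% and 73%. Section 9.1 accepts roughly 75% at one-sided 10% for the primary efficacy endpoint.

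**2. What baseline adjustment gains**

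Relative to unadjusted day-30 values, ANCOVA multiplies the variance by 1 − ρ². Relative to simple change from baseline, whose variance is 2(1 − ρ), the sample-size equivalent is 2(1 − ρ)/(1 − ρ²) = 2/(1 + ρ).

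| ρ | variance multiplier, 1 − ρ² | equivalent extra patients v day-30 values | equivalent extra patients v change score |
|---|---|---|---|
| 0.3 | 0.91 | 1/0.91 = 1.10, 10% | 2/1.3 = 1.54, 54% |
| 0.5 | 0.75 | 1/0.75 = 1.33, 33% | 2/1.5 = 1.33, 33% |
| 0.7 | 0.51 | 1/0.51 = 1.96, 96% | 2/1.7 = 1.18, 18% |

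**3. When missing baseline samples cancel the gain**

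If m patients per arm have both samples and 40 have a day-30 sample, adjustment is more precise when (1 − ρ²)/m < 1/40, that is m > 40(1 − ρ²). The break-even is 36.4, 30.0 and 20.4 pairs per arm at ρ = 0.3, 0.5 and 0.7.

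**4. Genotype**

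The aim in section 3 concerns how genotype changes aspirin's effect. A covariate alone estimates genotype's own association with the marker. A change in the treatment effect needs a treatment-by-genotype term, and either version needs a CSF model to exist.

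**The case against.** The case for leaving the plan alone has weight:

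- This is a pilot whose primary objective is to generate data, and section 9.2 admits limited power. The dose question is a rationale question, not a listed objective in section 4. The synopsis does not list CSF inflammation among its secondary endpoints. Section 5.2 lists 14 CSF markers (3 routine measures, 5 cytokines, 6 eicosanoids), and describing them is defensible. This lowers the severity but leaves the mismatch between sections 3 and 9.2.
- A reader might infer that the baseline CSF is discarded. The protocol does not say so. It stores the pre-treatment CSF, and resolution as an endpoint implies reference to an earlier value. What can be said is that no use of baseline is specified.
- A reader might infer that no between-arm comparison can be made. A descriptive analysis does not forbid a difference with an interval; none is planned.
- A reader might call the day-30 endpoint an error, because day-60 CSF is also taken. Choosing one time point is a preference.
- A reader might expect chance imbalance to be taken for a treatment effect. Randomisation is stratified by MRC grade, and a summary of change from baseline would display baseline levels, so this cannot be assumed.
- Follow-up CSF exists only in sampled survivors. Section 9.1 expects about 40% of controls to have an infarct or die by day 60, without giving deaths separately. A fitted model could suggest more causal precision than such data support. This objection stands, and the fix must allow for it.

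**Conclusion.** The point holds as a mismatch inside the protocol. Section 3 sets a comparative dose question and a genotype question on CSF inflammation, and section 9.2 fixes a method that plans neither the contrast nor the model.

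Small size does not excuse the omission, since 40 per arm gives ±0.44 SD unadjusted and ±0.42 to ±0.31 SD adjusted. These figures rest on assumed correlations, complete sampling and roughly normal log values, and they ignore any gain from MRC grade. At 28 per arm the unadjusted figure is ±0.52 SD.

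A reader might also infer that the added analysis would settle whether the doses act alike. It would not: intervals this wide cannot establish sameness unless a wide margin is accepted, and a non-significant difference is not evidence of it.

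Severity is minor to moderate. The primary endpoints are unaffected.

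**What to change.** Amend section 9.2 before unblinding:

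1. Analyse log-transformed day-30 CSF markers by ANCOVA, adjusted for the log baseline value and MRC grade. Report ratios with 95% confidence intervals for 1000 mg v 81 mg and for each dose v placebo.
2. Name PGE2 and PGD2 as the markers for the dose question. Label the other markers, and any day-60 analysis, exploratory.
3. Fit LTA4H genotype in this model, with a treatment-by-genotype term if effect modification is meant.
4. Report by arm the numbers with baseline and day-30 samples and the deaths before day 30. State that the estimates apply to sampled survivors.
5. State that a non-significant difference will not be read as equal effect.

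The cost is wording and routine programming on samples already being collected. The small downside is that baseline assays rely on residual CSF, so some patients will lack a baseline value. Under the protocol's rule of no imputation they would drop out of the adjusted model. Giving the unadjusted day-30 contrast beside it would show whether that matters.
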